## Abstract

**Background:**

Sensitive and reproducible detection of residual disease after treatment is a major challenge for patients with locally advanced head and neck cancer. Indeed, the current imaging techniques are not always reliable enough to determine the presence of residual disease. The aim of the NeckTAR trial is to assess the ability of circulating DNA (cDNA), both tumoral and viral, at three months post-treatment, to predict residual disease, at the time of the neck dissection, among patients with partial cervical lymph node response on PET-CT, after potentiated radiotherapy.

**Methods:**

This will be an interventional, multicentre, single-arm, open-label, prospective study. A blood sample will be screened for cDNA before potentiated radiotherapy and after 3 months if adenomegaly persists on the CT scan 3 months after the end of treatment. Patients will be enrolled in 4 sites in France. Evaluable patients, i.e. those with presence of cDNA at inclusion, an indication for neck dissection, and a blood sample at M3, will be followed for 30 months. Thirty-two evaluable patients are expected to be recruited in the study.

**Discussion:**

The decision to perform neck dissection in case of persistent cervical adenopathy after radio-chemotherapy for locally advanced head and neck cancer is not always straightforward. Although studies have shown that circulating tumour DNA is detectable in a large proportion of patients with head and neck cancer, enabling the monitoring of response, the current data is insufficient to allow routine use of this marker. Our study could lead to better identification of patients who do not have residual lymph node disease in order to avoid neck dissection and preserve their quality-of-life while maintaining their prospects of survival.

**Trial registration:**

Clinicaltrials.gov: NCT05710679, registered on 02/02/2023, https://clinicaltrials.gov/ct2/show/. Identifier with the French National Agency for the Safety of Medicines and Health Products (ANSM): N°ID RCB 2022-A01668-35, registered on July 15^th^, 2022.

## Background

With about 600 000 new cases per year, head and neck cancers (HNC) rank in 6^th^ position among the most common malignancies worldwide [1, 2]. More than half of the patients present a locally advanced stage at diagnosis [3]. The main risk factors for developing HNC are tobacco and alcohol consumption. High-risk papillomavirus (HPV) infection is also a cause of HNC, particularly for oropharynx cancer [4–6]. Despite treatment, 30 to 50% of patients relapse within 2 years and median survival does not then exceed one year [7–9]. The standard treatments for HNC are radiotherapy, surgery and chemotherapy [6].

Post-treatment follow-up of patients requires, among other things, a thorough clinical examination and repeated imagery investigations. The main difficulty lies in the interpretation of the results of these examinations as a result of post-operative and post-radiation changes that are difficult to distinguish from residual or recurrent tumour [10, 11].

The persistence of residual disease at the end of radiotherapy treatment is a major prognostic issue. 18F-fluorodeoxyglucose (FDG) positron emission tomography-computed tomography (PET-CT)-guided surveillance, with a negative predictive value of 95–97%, has proven to be non-inferior to cervical curage in CETEC with residual adenomegaly after radio-chemotherapy [12, 13]. Cervical curage is now indicated only if the response assessed by PET-CT is only partial. Nevertheless, the ability of PET-CT to predict residual disease is unsatisfactory because of a high frequency of false positives, due to inflammatory remodelling, with a positive predictive value of about 20–50% [14].

Currently, up to 50% of patients have residual adenomegaly after treatment, and only 30% have viable disease at the time of neck dissection [15, 16]. However, the acute and late complications to which patients who have undergone adenectomy are exposed are not negligible and can damage their quality-of-life (haemorrhage, scar disunion, alteration of swallowing function, etc.) [17–19].

Sensitive and reproducible detection of residual disease after treatment is a major issue for these patients. This is the context of our study, which aims to evaluate the prediction of residual disease using circulating DNA detection after potentiated radiotherapy for locally advanced head and neck cancer.

## Methods/design

### Study design

This interventional study is designed as a multicentre, single-arm, open-label, prospective study. The study has been registered on Clinicaltrials.gov (NCT05710679, 02/02/2023).

We expect to enrol 32 evaluable patients, i.e. with an indication for neck dissection and a blood sample at M3, to meet the primary objective. The enrolment period is expected to be 36 months. Each patient will be followed until two years after radiotherapy, reaching a total of 30 months.

### Coordination and participating institutions

The Centre Jean PERRIN (Clermont-Ferrand, France) sponsors the NeckTAR trial and is responsible for coordination, trial management, data management and trial monitoring.

This multicentre study is currently being conducted in 4 sites in France. The list of the study sites is available on https://clinicaltrials.gov/ct2/show/NCT05710679.

### Study objectives and endpoints

#### Primary objectives and endpoint

The primary objective of the study is to assess, at three months post-treatment, the ability of cDNA, tumoral and viral, to predict residual disease at the time of neck dissection among patients with partial cervical lymph node response after potentiated radiotherapy.

All patients with an indication for neck dissection will provide a blood sample for cDNA testing. To conclude on the diagnostic performance of post-treatment cDNA detection, we will compare the presence or absence of cDNA in the blood sample and the presence or absence of residual disease at the time of neck dissection (Fig. 1).

**Fig. 1 Fig1:**
[figure not shown]
Confusion diagram

#### Secondary objectives and endpoints

Assessment of the cDNA detection rate among patients with residual adenomegaly after treatment. This will be evaluated according to cDNA detection and response on CT-scan.

Assessment of the relationship between cDNA detection and metabolic lymph node response on PET scan after treatment among patients with residual adenomegaly. This endpoint will be evaluated according to cDNA detection and objective metabolic response at three months after potentiated radiotherapy.

Assessment of the prognostic value of cDNA detection 3 months after the end of potentiated radiotherapy for patients with residual adenomegaly. This endpoint will be evaluated using overall survival and progression-free survival.

Assessment of the prognosis value of the presence of residual adenomegaly. This will be evaluated using overall survival and progression-free survival.

Assessment of the concordance of mutational profiles and HPV-HR genotypes between the primary tumour and cDNA at diagnosis. This endpoint will be evaluated on the basis of the mutational profiles from FFPE blocks and the inclusion blood sample.

Assessment of concordance between p16 immunohistochemistry and HPV-HR genotyping on the primary tumour.

Test of the concordance between real-time PCR and NGS on FFPE blocks for simultaneous detection and genotyping of HPV-HR at diagnosis.

Assessment of the relationship between ctDNA and cvDNA detection at diagnosis and the clinical, paraclinical and pathological features of the cancer.

Assessment of inter-observer reproducibility of the interpretation of SUVmax measures of residual cervical adenomegaly. A centralized review of the initial and three months post-treatment PET-CT will be performed by the sponsor’s nuclear medicine department.

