### Participant eligibility

The exhaustive list of selection criteria is presented in Table 1. Patients with a recent diagnosis of locally-advanced head and neck cancer with lymph node involvement and never previously treated and for whom potentiated radiotherapy is indicated are eligible. After the signature of informed consent, a blood sample will be taken (2 tubes of 9 mL) and a FPPE block (from the tumour or a lymph node biopsy) will be recovered and sent to the sponsor. Centralized analyses will be conducted to identify specific tumour mutations on FFPE blocks and to search for the presence of cDNA in the blood sample. Patients for whom neither specific tumour mutations nor cDNA is found will be considered as screening failures.

**Table 1 Tab1:** Selection criteria

Inclusion criteria	Non-inclusion criteria
Age ≥ 18 and ≤ 80 years old	Tumor of the nasopharynx, sinuses, nasal cavity, salivary glands or thyroid cancer
Epidermoïd carcinoma histologically confirmed, never treated, with lymph node envolvment	Treatment with radiotherapy only
Stage III (N1), stage IVa (minimum N1) or IVb, resectable but not operated or unresectable, with potentiated radiotherapy indication	Contraindication for neck dissection
Oral cavity, oropharynx, hypopharynx or larynx, cervical adenopathies without a primitive	Metastatic disease (stage IVc)
Tumoral sample FFPE available before the treatment initiation	History of treatment for a head and neck cancer
Presence of cDNA in the initial blood sample	History of other cancer within 3 years (except carcinoma in situ, basal cell skin carcinoma, localized prostate cancer Gleason 6)
Tumor-specific variant detected on FFPE and leucocytes	Pregnant or breastfeeding woman
Written informed consent signed	Patient under guardianship or curatorship
Affiliation to the French social security system	Psychological disorder (cognitive disorders, mental alertness, etc*.*) or social (deprivation of liberty by judicial or administrative decision) or geographical reasons that may compromise medical monitoring of the trial or compliance with treatment

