#### Analyses of secondary endpoints

Secondary analyses will be performed primarily on all patients (regardless of indication for neck dissection), and also in the subgroup of patients with an indication for neck dissection (as for the primary objective).

The relationship between ctDNA/cvDNA detection at 3 months post-treatment and the treatment failure rate, as well as the relapse rate during follow-up, will be evaluated using the classic diagnostic performance measures calculated on contingency tables (including PPV, NPV, sensitivity, specificity, overall accuracy). In addition, for concordance analyses (of binary variables) between ctDNA/cvDNA and primary tumour, between p16 IHS and real-time PCR, and between real-time PCR and NGS, Cohen's kappa method will also be used.

Survival will be analysed using Kaplan–Meier curves (and log-rank test if relevant). The prognostic value of the presence of residual adenomegaly will be assessed using a Cox model. Other prognostic factors for survival will be investigated using firstly univariate Cox models, and then multivariate models to assess the prognostic value of the presence of residual adenomegaly in particular, and to identify possible confounding factors. For patients with ct/cvDNA collection and analysis at 3 months after the end of treatment, the prognostic impact of ct/cvDNA detection at 3 months in particular will be analysed.

The relationship between ctDNA/cvDNA detection at diagnosis and the clinical, para-clinical and pathological characteristics of the cancer will be performed using McNemar's test, Wilcoxon's signed rank test, Spearman's correlation and multiple linear or logistic regression models, depending on the type of data.

Inter-observer reliability will be assessed using Cohen's kappa method on three-level criteria (positive, doubtful lymph node involvement, or negative).

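### Selecting on baseline cDNA leaves any-cDNA detection at diagnosis constant and tilts tumour–plasma concordance upward; both baseline objectives should use all screened patients

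*Protocol article*

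**What the plan says.** All references are to the Protocol article.

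- **Secondary objectives and endpoints** contains two objectives that rest on the blood sample at diagnosis. Objective A is "Assessment of the relationship between ctDNA and cvDNA detection at diagnosis and the clinical, paraclinical and pathological features of the cancer". Objective B is "Assessment of the concordance of mutational profiles and HPV-HR genotypes between the primary tumour and cDNA at diagnosis".
- **Participant eligibility, Table 1** lists among the inclusion criteria both "Presence of cDNA in the initial blood sample" and "Tumor-specific variant detected on FFPE and leucocytes".
- The **text above Table 1** words the exclusion differently: "Patients for whom neither specific tumour mutations nor cDNA is found will be considered as screening failures". It also places consent, the blood draw, FFPE retrieval and the central assays before that decision.
- **Sample size calculations** expects 85% of patients to have detectable ct/cvDNA and moves from 63 patients to about 75 screened on that basis.
- **Analyses of secondary endpoints** sets the population: "Secondary analyses will be performed primarily on all patients (regardless of indication for neck dissection". It adds Cohen's kappa "for concordance analyses (of binary variables) between ctDNA/cvDNA and primary tumour" and, for objective A, lists paired and correlation tests and linear or logistic regression, depending on data type.
- The **Abstract** defines cDNA as a composite: it speaks of the "ability of circulating DNA (cDNA), both tumoral and viral, at three months post-treatment".

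**The concern.** Objective A needs patients with and without detection at diagnosis. Objective B needs patients whose plasma does and does not reflect the tumour. Table 1 removes patients with no signal in plasma before they join the study, and the secondary-analysis population is widened only with respect to neck-dissection indication; nothing brings screening failures back in. If the analysis is run that way, one form of objective A has no contrast at all, and objective B is computed in patients chosen partly because their plasma was positive. A reader of the final report could then take an inflated concordance as describing locally advanced head and neck cancer at diagnosis, when it describes only those who shed detectable DNA. If baseline data on screening failures are not kept prospectively, this may not be repairable afterwards.

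**Working it through.** **1. The plan's funnel, reproduced.** Inputs from Sample size calculations: 28 patients with an indication, 50% indication rate, 10% attrition, 85% detectable.

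- 28 / 0.50 = 56
- 56 / 0.90 = 62.2, rounded up to 63
- 63 / 0.85 = 74.1, rounded up to 75

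All match the plan. Of 75 screened, 75 × 0.85 = 63.75 (about 64) would have detectable cDNA and 75 × 0.15 = 11.25 (about 11) would not. The 63 and 64 differ only by rounding.

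**2. Objective A, any cDNA.** Under Table 1 the included set has 63 positive and 0 negative patients. A table of detection by any feature has an empty row, and a logistic model for detection has a constant outcome. No association can be estimated.

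**3. Objective A, each marker separately.** Cross-classify the included patients:

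| | cvDNA+ | cvDNA− |
|---|---|---|
| ctDNA+ | possible | possible |
| ctDNA− | possible | empty by Table 1 |

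Both margins can vary, so a contrast survives. For an assumed cvDNA-positive share of 10%, 20%, 30% or 50% of 63, the split is 6/57, 13/50, 19/44 or 32/31. A feature present in 40% of cvDNA-negative and 80% of cvDNA-positive patients (assumed) would be found with power of about 0.46, 0.77, 0.87 and 0.92 (two-sided 5%, formula in step 6). But the empty cell means that every ctDNA-negative patient is cvDNA-positive, and that ctDNA detection is 100% among cvDNA-negative patients. The ctDNA contrast is therefore tied to viral status by selection.

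**4. Objective B, kappa.** κ = (p_o − p_e) / (1 − p_e).

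- *Any tumour variant against any plasma signal, per patient.* All 63 fall in one cell, so p_o = p_e = 1 and κ = 0/0.
- *Tumour variant always present, plasma not always* (for example ctDNA alone, with 58 of 63 positive for illustration). p_o = 58/63 and p_e = (63 × 58 + 0 × 5)/63² = 58/63, so κ = 0 whatever the agreement. Specificity and NPV cannot be estimated.
- *HPV in tumour against cvDNA.* Negatives remain, so κ is estimable. Suppose 19 of 63 tumours are HPV-positive and two of these are cvDNA-negative. Then p_o = 61/63 = 0.968, p_e = (19 × 17 + 44 × 46)/63² = 0.591 and κ = 0.92. With 6, 13 or 32 HPV-positive tumours it is 0.78, 0.90 or 0.94.

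**5. Size of the bias in objective B.** Let c be the average share of tumour findings recovered in plasma among included patients. Those excluded for undetectable cDNA recover none.

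- If all of the excluded 15% have tumours carrying a panel variant or HPV, the value in all screened patients is 0.85c. The overstatement is 0.15c, at most 15 percentage points.
- If none of them do, they have no tumour finding to recover, and the overstatement of this measure is zero.

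The document does not say where between these the excluded patients lie.

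**6. What the screened set would offer objective A.** With n₁ = 64 detected, n₂ = 11 not detected, feature prevalences p₁ and p₂ and pooled prevalence p̄:

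power = Φ[(|p₂ − p₁| − 1.96·SE₀)/SE₁], where SE₀ = √[p̄(1 − p̄)(1/n₁ + 1/n₂)] and SE₁ = √[p₁(1 − p₁)/n₁ + p₂(1 − p₂)/n₂].

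For 40% against 80%: p̄ = (25.6 + 8.8)/75 = 0.459, SE₀ = 0.163, SE₁ = 0.135, and power = Φ(0.60) = 0.73. For 40% against 60%, 70% and 90% it is 0.23, 0.45 and 0.95. The prevalences are assumed, and the normal approximation is rough with 11 patients.

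**The case against.** The strongest reply has four parts.

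- **The objectives are not about any cDNA.** A reader might infer that both objectives are unanswerable because nothing varies. The document does not support that. Objective A names ctDNA and cvDNA, and each can vary among patients positive for either. Objective B is about which variants and genotypes match, and these differ between patients; HPV concordance keeps its negatives. Kappa for mere presence in each compartment is one possible reading of the binary variables, which the article does not define. All of this stands. It does not remove the selection described in steps 3 and 5.
- **Screening failures may not be what Table 1 implies.** Read literally, the sentence above Table 1 fails a patient only when both findings are absent, so a plasma-negative patient with a tumour mutation would stay in and supply contrast. This stands as a contradiction within the document. The Abstract's definition of evaluable patients and the step from 63 to 75 both follow Table 1, so the problem cannot be dismissed on that sentence.
- **The 15% is a non-detection rate.** A reader might infer that concordance will be overstated by 15 points. The 15% is not a tumour–plasma disagreement rate, and it may include patients whose tumours carry nothing the panel can find. This stands.
- **Analysis sets belong in the SAP.** In general they do, and the article is silent on whether screened patients count among all patients. But here the inclusion criteria and two stated objectives pull against each other within the protocol itself, and the remedy depends on data that must be collected prospectively.

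**Conclusion.** The point holds in a limited form. On Table 1, with secondary analyses confined to included patients:

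- the relation of any-cDNA detection at diagnosis to cancer features cannot be estimated (63 of 63 positive);
- the ctDNA and cvDNA contrasts can be estimated, but on a set shaped by selection;
- concordance of profiles and genotypes can be estimated but tends to be overstated;
- a per-patient kappa for presence of any tumour variant against any plasma signal, if that is what is meant, is undefined, and it is zero if only the plasma side varies.

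The size of the overstatement is unknown. The bound of 15 points needs the assumption that all of the roughly 11 excluded patients have tumours with a panel variant or HPV. The conclusion also assumes that Table 1, rather than the looser screening-failure sentence, governs inclusion, and that all patients means included patients. The primary PPV analysis and the sample size are unaffected. This is worth correcting because the remedy is cheap, but it concerns secondary objectives only.

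**What to change.** 1. State that objectives A and B are analysed on all consented, screened patients with baseline plasma and FFPE results, including screening failures. Keep the included set for the other secondary analyses.
2. Retain the baseline clinical, paraclinical and pathological data of screening failures in the eCRF.
3. Reconcile Table 1, which requires both criteria, with the sentence that fails a patient only when neither is found.
4. Define the binary variables for kappa by variant or genotype rather than as presence of any signal, and describe the feature analysis as exploratory.

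The cost is protocol and SAP wording plus baseline data on about 11 more patients. Consent, blood and tumour assays already precede the screening-failure decision, so no new patient procedure is needed. The limit is precision: about 64 against 11 patients has good power only for large differences.

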### Participant eligibility

The exhaustive list of selection criteria is presented in Table 1. Patients with a recent diagnosis of locally-advanced head and neck cancer with lymph node involvement and never previously treated and for whom potentiated radiotherapy is indicated are eligible. After the signature of informed consent, a blood sample will be taken (2 tubes of 9 mL) and a FPPE block (from the tumour or a lymph node biopsy) will be recovered and sent to the sponsor. Centralized analyses will be conducted to identify specific tumour mutations on FFPE blocks and to search for the presence of cDNA in the blood sample. Patients for whom neither specific tumour mutations nor cDNA is found will be considered as screening failures.

**Table 1 Tab1:** Selection criteria

Inclusion criteria	Non-inclusion criteria
Age ≥ 18 and ≤ 80 years old	Tumor of the nasopharynx, sinuses, nasal cavity, salivary glands or thyroid cancer
Epidermoïd carcinoma histologically confirmed, never treated, with lymph node envolvment	Treatment with radiotherapy only
Stage III (N1), stage IVa (minimum N1) or IVb, resectable but not operated or unresectable, with potentiated radiotherapy indication	Contraindication for neck dissection
Oral cavity, oropharynx, hypopharynx or larynx, cervical adenopathies without a primitive	Metastatic disease (stage IVc)
Tumoral sample FFPE available before the treatment initiation	History of treatment for a head and neck cancer
Presence of cDNA in the initial blood sample	History of other cancer within 3 years (except carcinoma in situ, basal cell skin carcinoma, localized prostate cancer Gleason 6)
Tumor-specific variant detected on FFPE and leucocytes	Pregnant or breastfeeding woman
Written informed consent signed	Patient under guardianship or curatorship
Affiliation to the French social security system	Psychological disorder (cognitive disorders, mental alertness, etc*.*) or social (deprivation of liberty by judicial or administrative decision) or geographical reasons that may compromise medical monitoring of the trial or compliance with treatment

### Blood sample for cDNA research

Each participant will provide a blood sample at inclusion, before the initiation of potentiated radiotherapy. Then, at the three-month evaluation of the disease, a second blood sample will be collected for the patients with residual lymph nodes on the scan.

After DNA extraction, a specific panel, defined previously and including the main mutation of head and neck cancer and HPV, will be applied to each of the samples to search for specific HNC mutations on ctDNA.

